## **2.1 Primary Objective**

To determine whether 12 weeks of periodized RT improves cerebrovascular function in healthy older adults. Cerebrovascular function will be evaluated by resting CBF, intracranial vascular compliance, and arterial transit time (ATT), assessed using ASL MRI techniques. This study will establish response variance and effect sizes while generating preliminary signals of efficacy in an aging related outcome.

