## **2.3 Exploratory Objectives**

1. To determine whether changes in cerebrovascular function mediate the relationship between RT and improvements in cognition.

2. To evaluate intervention effectiveness and explore potential mechanisms of benefit using various physical, physiological, and biochemical outcomes. These outcome measures include: 1) physical capacity (muscle strength and maximal oxygen consumption), body composition, and functional mobility; 2) putative blood markers of exercise-induced brain plasticity (i.e. BDNF, IGF-1, and VEGF); 3) cardiovascular risk factors (i.e. blood pressure) and markers of endothelial dysfunction (i.e. tissue plasminogen activator (t-PA) and Von Willebrand factor (VWF)); and 4) brain morphology (e.g. volume, cortical thickness, and white matter lesions) and resting state brain activity.

3. To investigate associations between brain adaptations and potential mechanisms of benefit. Changes in the above outcome measures will be examined for their roles in mediating RT-induced changes in cognition and cerebrovascular function.

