# **13.0 Statistical Considerations**

## **13.1 Statistical Analysis Plan**

Participant characteristics will be described at baseline. Continuous variables will be examined for normality and described by either means and standard deviations or medians and interquartile range (if not normal); categorical variables will be described with N (%) of each category. Participant characteristics will be compared with missing data and attrition to determine if there are any systematic patterns that should be adjusted for in secondary analyses; any difference with p < 0.25 will be used in secondary analyses to see if there is an effect on the intent-to-treat model.

Comparison of cerebrovascular function (Hypothesis 1) and cognition (Hypothesis 2) between groups will follow intent-to-treat models using longitudinal linear mixed effects modeling to assess the change in these outcomes, with the main factor of period – control versus RT. The stratifying factor of gender will also be included in the model, as is standard. This same modeling will be used to test whether cerebrovascular function mediates the effect of group assignment on cognition by adding cerebrovascular function to the model of cognition and examining the change in the beta coefficient of group (exploratory objective 1). A change in beta coefficient of >20%, will be considered indicative of mediation. Because these data will be preliminary, the primary endpoint will be the effect size calculated from the estimated marginal means of differences in the change by period from the models. This can then be translated more directly into potential clinical effect.

This same modeling technique will be used for outcomes defined in exploratory objective 2. To assess the association of changes in cerebrovascular function and cognition with other outcomes (exploratory objective 3), Spearman correlations of change in outcomes, adjusted for baseline level will be computed for the total group, and stratified by group assignment.

All analyses will be performed with SPSS (v.24).

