## **13.2 Sample Size and Power Considerations**

Because this is a proof-of-concept clinical trial, sample size will be determined based on feasibility and study funding. Previous investigations on CBF after 12 weeks of aerobic exercise [47] suggest that 20 participants per group is sufficient to determine response variance and effect sizes to establish preliminary signals of efficacy. Attrition rate is anticipated to be 15%, a conservative estimate, as the attrition rate of previous RT interventions of similar length (12 weeks, 3days/week) in healthy older adults is about 5.7% [131]. Our previous RT intervention in older adult men, upon which the current study’s RT program is based, had no dropouts due to injury, illness, or personal choice [80]. Accounting for 15% attrition (~3) yields a final, proposed sample size of 23.

Sensitivity analysis using these parameters was performed in G*Power 3.1.9.2. With the proposed sample size of 23, we would have sufficient power to statistically detect a large effect size d between dependent means of 0.611 with α = 0.05 and 1-β = 0.80.

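### The rule that a change of more than 20% in beta indicates mediation makes no allowance for sampling error, so with about 20 completers its false-declaration rate is uncontrolled

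*Protocol*

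**What the plan says.** Section 13.1 plans a longitudinal linear mixed model for cerebrovascular function and cognition, "with the main factor of period – control versus RT", and adds: "The stratifying factor of gender will also be included in the model, as is standard". Mediation is to be examined by "adding cerebrovascular function to the model of cognition and examining the change in the beta coefficient of group (exploratory objective 1"). The decision rule follows: "A change in beta coefficient of >20%, will be considered indicative of mediation". Nothing is said about an interval, a test, the direction of the change, or any condition on the period effect.

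The question is exploratory objective 1 in section 2.3: "To determine whether changes in cerebrovascular function mediate the relationship between RT and improvements in cognition". Section 2.1 supplies three candidate mediators: "Cerebrovascular function will be evaluated by resting CBF, intracranial vascular compliance, and arterial transit time (ATT), assessed using ASL MRI techniques". Section 2.2 supplies individual cognition scores and three composites.

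On size, section 13.2 refers to earlier work said to "suggest that 20 participants per group is sufficient to determine response variance and effect sizes", and then: "Accounting for 15% attrition (~3) yields a final, proposed sample size of 23". It gives a detectable paired effect of 0.611 for 23 participants. No effect is assumed for any mediator or cognition score, and no error rate is given for the mediation rule.

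**The concern.** The criterion is a ratio. Its denominator is the estimated period effect on cognition, which may be close to zero. Its numerator contains the fitted slope of cognition on the mediator, and in about 20 people that slope is rarely zero even when the two are unrelated. If training moves the mediator, the chance slope passes into the adjusted coefficient and can look like mediation. As worded, a rise in the coefficient (suppression) counts as much as a fall.

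Section 2.0 presents the study as an investigation of the vascular processes behind cognitive gain. A mediation label that appears or disappears by chance would bear directly on that message and on the choice of mechanism for a later trial.

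**Working it through.** **The protocol's own figure.** For a paired t-test with n = 23, two-sided α = 0.05 and d = 0.611, the noncentrality is 0.611 × √23 = 2.93 on 22 degrees of freedom. Power is 0.7996, and the detectable effect at 80% power is 0.6113. The stated 0.611 reproduces. Also, 20 × 1.15 = 23.

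**The rule as a formula.** For each participant, let Y be the change in cognition under training minus the change in the control period, and let M be the same difference for the mediator. Then

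- c = mean(Y), the period effect
- b = slope of Y on M
- c′ = mean(Y) − b × mean(M), the period effect after adjustment
- relative change = (c − c′)/c = b × mean(M)/mean(Y); the rule fires if its absolute value exceeds 0.20.

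**Hand check.** Express effects in standard deviations of Y and M and set both true means to 0.611. They cancel, and the rule becomes |b| > 0.20. With no link between mediator and cognition and n = 20, the standard error of b is about 1/√(20 − 3) = 0.243. The cut-off is 0.20/0.243 = 0.82 standard errors, which chance exceeds about 41% of the time.

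**Simulation with no mediator-to-cognition path, n = 20.** All effects are assumptions, because the protocol gives none. Model A is the paired-difference model above (40,000 replicates per row). Model B is a random-intercept REML model on the two change scores with period, gender and mediator (1,500 replicates per row).

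| Mediator effect | Cognition effect | Either direction, A / B | Attenuation only, A / B |
|---|---|---|---|
| 0 | 1.0 | 1.4% / 0.8% | 0.7% / 0.5% |
| 0 | 0.611 | 7% / 4% | 4% / 2% |
| 0.3 | 0.611 | 18% / 13% | 9% / 7% |
| 0.611 | 0.611 | 39% / 29% | 20% / 14% |
| 0.3 | 0.4 | 32% / 24% | 16% / 12% |
| 0.611 | 0.4 | 55% / 47% | 28% / 25% |
| 0.611 | 0.2 | 71% / 64% | 35% / 32% |
| 1.0 | 0 | 87% / not run | 44% / not run |

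With all 23 participants, rates are at most about 4 points lower.

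**Mediator correlated with cognition but not moved by training** (also no mediation; residual correlation 0.5, model A, either direction): 64% at a cognition effect of 0.2, 46% at 0.4, 29% at 0.611 and 11% at 1.0.

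**Several measures.** Take one cognition score, three mediators, all effects 0.611 and no mediation. At least one false flag then occurs in 67% of trials (mediators correlated 0.5) to 73% (independent) counting either direction, and in 37% to 46% counting attenuation only (model A).

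**The case against.** Much can be said for leaving the rule alone. The objective is exploratory, the study is sized on feasibility, section 13.1 calls the data preliminary, and the cut-off is only said to be indicative. Mediation normally means attenuation, which about halves the rates. A sensible analyst would look for mediation only after seeing cognition improve. If a statistically significant improvement were required first, improvement with attenuation above 20% would occur in about 11% of trials when both effects are 0.6, and in 0.1% when there are no effects at all. The training effect on cerebrovascular function is estimated separately under Hypothesis 1, so a reader would see whether the mediator moved.

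These points lower the severity. They do not rescue the rule, because neither the restriction to attenuation nor the prior condition on cognition is written down. Exploratory status excuses low power and the absence of alpha control, but not a yes/no label without uncertainty.

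Two stronger readings are not supported. A reader might infer that the rule would falsely declare mediation in some fixed share of trials, such as 25% to 60%. The protocol states none of the effects needed for that, and both ends can be passed: 7% or less in the second row of the table, 71% in the seventh. A reader might also take the word group as a contradiction in a one-group design. The same paragraph names period as the factor, so this is an editorial leftover.

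**Conclusion.** The concern holds in conditional form. The 20% rule is fully specified and is a poor decision rule at this sample size. With no mediation present, it flags a single mediator-cognition pair in about 1% to 87% of trials, depending on effects the protocol does not give. The most relevant benchmark is the protocol's detectable effect of 0.611 for both mediator and cognition. There the rate is 29-39% as worded and 14-20% if only attenuation counts, the lower figure of each pair coming from the model closer to the planned one. It falls to 4-7% when the mediator is unmoved and unrelated and the cognition effect is 0.611.

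These figures rest on normally distributed data, about 20 completers and the assumed effects shown. Severity is minor to moderate: no primary or secondary conclusion depends on the rule.

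**What to change.** In section 13.1, drop the 20% cut-off as the criterion and replace it as follows.

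- Estimate the indirect effect of period (training versus control) through the within-person change in the mediator: the period effect on the mediator times the mediator's coefficient in the cognition model. Keep gender and the planned mixed model. The paired-difference version can serve as a check.
- Report it with a percentile-bootstrap 95% confidence interval, resampling whole participants, and label it exploratory.
- Describe a mediation signal only if the interval excludes zero in the direction of attenuation. Give the percentage change in beta as description only.
- Report every mediator-cognition pair examined, since the interval does not deal with multiplicity.
- Replace group by period.

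The cost is one paragraph and a short script, with no new data or visits. In the paired-difference version, the bootstrap interval was falsely positive in 0.3% to 6% of trials over five no-mediation scenarios; the mixed-model version was not simulated.

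The real price is power. With true mediation and n = 20, the interval excluded zero in about 6% of trials when both paths were 0.3, about 17% when both were 0.4, and somewhat under half when they were 0.6 and 0.5. Few or no mediation claims are likely, and the protocol should say so.

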# **3.0 Study Design**

This study will be conducted in the Clinical Exercise Research Center (CERC) in the Division of Biokinesiology and Physical Therapy on the University of Southern California Health Sciences Campus. In this mechanistic proof-of-concept clinical trial, the effects of a 12-week periodized RT intervention on the brain will be compared to that of an initial control period of equal duration. After baseline testing, participants will be asked to resume normal life for the 12-week control period. After the control period, and before the RT intervention, participants will undergo the same tests performed at baseline. Post-intervention, participants will be tested again (please see study calendar 9.10).

**Study Visit 1:** Interested participants will report to the CERC and read the informed consent with a study investigator. The prospective participant will be given the opportunity to ask any questions they may have about the study. If the potential subject is willing to take part in the study, she/he will sign the informed consent agreeing to participate. She/He will also complete a Physical Activity Readiness Questionnaire (PAR-Q) to ensure she/he is at a baseline fitness level necessary for exercise training, and a Mini-Mental State Examination (MMSE) to screen for cognitive deficits. All potential subjects will have their blood pressure taken during this visit to ensure normal levels. Additional screening will take place, according to the inclusion/exclusion criteria.

**Study Visit 2 (Baseline Testing Part 1):** All participants will undergo the following tests: cognitive testing, quality of life questionnaires, and MRI scans. Approximate time: 2.5 hours

**Study Visit 3 (Baseline Familiarization Day):** Descriptive factors will be measured on all participants. Then they will undergo exercise and testing familiarization. Approximate time: 1.5 hours

**Study Visit 4 (Baseline Testing Part 2):** All participants will undergo the following tests: International Physical Activity Questionnaire (IPAQ), blood pressure, body composition, blood draw, Physical Function tests, Muscle Strength tests, and estimated VO2max tests. Approximate time: 2.5 hours

**Control Period:** Participants will be encouraged to continue normal activities of daily living and eating routines.

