# **6.0 Randomization Scheme**

No randomization will be necessary. Participants will serve as their own controls, and therefore will all receive supervised RT. The 12-week control period will be done before the RT intervention to ensure that results are not confounded by a detraining effect. In addition, long-term cognitive benefits after exercise interventions have been found up to two years follow-up [88, 89].

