## **16.2 Financial Obligations and Compensation**

There are no financial obligations on the part of the subject. There will be no financial compensation for participation in this study. However, participants will receive supervised RT or flexibility training by a certified exercise specialist.

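### The Objective 3 correlations are specified by a group assignment that the trial does not have, and if group is read as period, the total-group correlation pools two linked changes per person and can show association between unrelated outcomes

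*Protocol*

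**What the plan says.** Section 13.1 gives the rule for objective 3: "Spearman correlations of change in outcomes, adjusted for baseline level will be computed for the total group, and stratified by group assignment". Section 2.3 states what the correlations are for: "Changes in the above outcome measures will be examined for their roles in mediating RT-induced changes in cognition and cerebrovascular function".

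Section 6.0 describes the allocation: "No randomization will be necessary. Participants will serve as their own controls, and therefore will all receive supervised RT". The mixed model in section 13.1 accordingly compares periods, "with the main factor of period – control versus RT".

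Section 3.0 adds a second measurement before training: "After the control period, and before the RT intervention, participants will undergo the same tests performed at baseline". With the post-intervention tests, each person therefore has two changes: a control change (pre-intervention minus baseline) and an RT change (post-intervention minus pre-intervention).

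The protocol does not say which of these enters the total-group correlation, how two changes from one person would be handled, or whether baseline level means the week 1-2 value or the value at the start of the period concerned.

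**The concern.** The sentence belongs to a parallel-group trial. Section 16.2 carries another trace of such a design: "participants will receive supervised RT or flexibility training by a certified exercise specialist". In a parallel-group trial each person has one change, and strata by arm are well defined. Here the stratifying variable does not exist, so the analyst has to reinterpret the sentence.

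The natural reinterpretation is to replace group by period, because period is the contrast in the main model and the only reading that gives the strata a meaning. The total group then consists of all control changes and all RT changes together. Two problems follow. The two changes of one person share the pre-intervention measurement and are not independent. More seriously, if both outcomes are on average higher in the RT period, the pooled points form two clouds displaced in the same direction, and the displacement alone produces a correlation.

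The trial calls itself mechanistic. The artefact would be largest when training moves both outcomes, which is also when a claim about mechanism would be made.

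**Working it through.** **Inputs from the protocol.** Sample size: "Accounting for 15% attrition (~3) yields a final, proposed sample size of 23". Detectable effect: "large effect size d between dependent means of 0.611 with α = 0.05 and 1-β = 0.80". Section 1.4 expects both cerebrovascular function and cognition to improve with RT.

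**Assumptions not in the protocol.** The correlation between visits is 0.8, the two outcomes are unrelated within persons, and mean shifts between periods are varied as shown below. The false-positive rate refers to a nominal two-sided 5% test. The protocol sets no such threshold for these correlations, so the rate is only a yardstick.

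**Step 1: reproduce the plan's figure.** A two-sided paired t-test with n = 23, α = 0.05 and power 0.80 has a detectable standardised difference of 0.6113 (noncentral t). The stated 0.611 is reproduced.

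**Step 2: express that effect as a shift between periods.** 0.611 is in units of the SD of the within-person difference between the two changes. If the correlation between a person's two changes is r, the shift in units of the SD of change is 0.611 × √(2(1 − r)). For a stable level plus measurement noise, r = −0.5 because the pre-intervention value is shared, and the shift is 0.611 × √3 = 1.058.

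**Step 3: expected pooled correlation of two unrelated outcomes.** With shifts a and b in SD of change and equal numbers per period,

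ρ = (ab/4) / √[(1 + a²/4)(1 + b²/4)].

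- a = b = 1.058: 0.280/1.280 = 0.22.
- a = b = 0.61: 0.0930/1.0930 = 0.09.
- a = 2, b = 0.6: 0.30/√(2 × 1.09) = 0.20.
- a = 2, b = 1: 0.50/√(2 × 1.25) = 0.32.
- Either shift zero: 0.

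For two outcomes that each shift by 0.611 in the protocol's units, the value depends on r: 0.22 at r = −0.5, 0.16 at r = 0 and 0.09 at r = +0.5.

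**Step 4: simulate with the planned adjustment.** Each replicate has three visits and a Spearman partial correlation adjusted for each outcome's value at the start of the period.

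| n | Shifts (SD of change) | Mean pooled correlation | Pooled, nominally significant | RT period only, nominally significant |
|---|---|---|---|---|
| 20 | 0 and 0 | 0.00 | 6% | 5% |
| 20 | 0.61 and 0.61 | 0.09 | 10 to 11% | 5% |
| 20 | 2 and 0.6 | 0.22 to 0.23 | 30 to 31% | 5% |
| 20 | 2 and 1 | 0.35 | 60 to 61% | 5% |
| 23 | 1.06 and 0 | 0.00 | 7% | 5% |
| 23 | 1.06 and 1.06 | 0.24 | 37 to 38% | 5% |

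Ranges reflect repeated runs. The control period alone also gives 5%. Adding period to the pooled adjustment brings the mean back to 0.00 with about 6% significant; the excess over 5% comes from treating two linked changes as independent. Adjusting for baseline level therefore leaves the artefact in place, while adjusting for period, or analysing within period, removes the displacement.

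**Step 5: check that the RT-period change can be formed.** Section 9.5 places blood draws at baseline and post-intervention only, and section 16.1 counts two draws. Section 9.4 places physical function tests at baseline and post-intervention. Study Visit 6 in section 3.0 and the calendar in section 9.10 schedule both pre-intervention as well. Under 9.4 and 9.5 there is no pre-intervention value, and so no change specific to either period, for these outcomes.

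**The case against.** The strongest reply is that the protocol never says it will pool. Total group could mean all participants with one change each. Section 10.0 defines endpoints by baseline and post-intervention measurements, and sections 9.4 and 9.5 describe two time points, which fits a single post-minus-baseline change. In simulation that reading gives a mean correlation of 0.00 and about 5% false positives. This stands: pooling is the most coherent reading but not a stated one. It does not rescue the sentence, because with one change per person the strata by group assignment have no meaning.

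Second, if group means period, the stratified correlations are the separate RT-period and control-period analyses, and these are sound. This also stands. The defect is confined to the total-group value.

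Third, the large figures depend on assumed shifts. The 2 SD shift is an illustration for an outcome such as strength and is not in the protocol. With both shifts at 0.61 SD of change the rate is 10 to 11%, and if only one outcome shifts the mean is zero. A reader might infer that the pooled analysis would mostly report an artefact whatever the results. The documents do not support that.

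Fourth, this is the last exploratory objective, the data are called preliminary, and no decision rests on these correlations. That limits the consequence. Section 13.1 does speak of association, but section 2.3 speaks of mediation, so a mechanistic interpretation is invited. The flexibility-training phrase in section 16.2 is consistent with leftover text but says nothing about which change is to be analysed.

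**Conclusion.** The concern holds in a limited form. Section 13.1 fixes the objective 3 analysis on a variable that the trial lacks, and the sentence needs correcting under any reading. Under the reading that makes the strata meaningful, the total-group correlation pools two dependent changes per person, and for unrelated outcomes it is biased away from zero whenever both shift between periods. Planned adjustment for baseline level does not remove this.

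The size depends on the shifts. At an assumed visit correlation of 0.8, the nominal false-positive rate runs from about 6% with no shift to 37 to 38% when both outcomes move by the protocol's detectable effect (n = 23), and to about 60% for assumed shifts of 2 and 1 SD of change (n = 20).

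Two stronger conclusions are not supported: that the protocol prescribes pooling, and that the primary result is at risk. The primary endpoint is an effect size from the period model and is unaffected. The correction is worth making because the trial's purpose is mechanistic and the remedy is small.

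**What to change.** In section 13.1:

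- Drop the total-group correlation and replace group assignment by period.
- Make the RT-period change (post-intervention minus pre-intervention), one value per participant and adjusted for the pre-intervention level, the objective 3 analysis. Report the control-period correlation beside it as a reference, adjusted for the week 1-2 level.
- If a pooled version is kept, require adjustment for period and a method that allows for repeated measures on the same person.

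In section 2.3, describe objective 3 as association rather than mediation.

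Reconcile sections 9.4, 9.5 and 16.1 with Study Visit 6 and the calendar in section 9.10, because the RT-period change needs a pre-intervention value. If any outcome has none, state that its RT-period correlation cannot be computed.

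The analysis changes cost a sentence or two of wording and no extra participants. Whether the reconciliation alters the test schedule depends on which passages reflect the intended visits.
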